### **11.2 Statistical analysis plan**

#### **11.2.1 Statistical Analysis Set**

The analysis sets defined in this study are as follows:

1) Full Analysis Set (FAS, Full Analysis Set)

2) Defined as all randomized subjects who had a baseline primary efficacy evaluation, took at least 1 dose of study drug. Subjects who take the drug which are not randomly assigned will be placed in randomly assigned group according to ITT. Per Protocol Set (PPS, Per Protocol Set)

Includes only subjects completing the study drug treatment, without major protocol deviation, completing the primary endpoint efficacy evaluation. PPS is defined as follow PPS populations be defined as follow

- Qualify for the inclusion criteria
- Completion of study treatment and follow up visit per protocol, fill in the content required in eCRF;
- Non concomitant medications which possibly affect the study drug's efficacy during the clinical trial.
- Compliance to the protocol

FAS and PPS are mainly used for efficacy analysis.

3) Safety Analysis Set (SS, Safety Set)

Includes all randomized subjects who have received at least one study drug. Subjects who take the drug which are not randomly assigned will be placed in actual treatment group according to the ASaT (Analysis as Treated) principle.

The above analysis data set will be discussed and decided by the main investigator, sponsor, statistician and data management before the database lock.

## 11.2.2 Statistical analysis method

### 11.2.2.1 General principles

All significant testing will be two-sided, unless otherwise specified. Data will be summarized using descriptive statistics number of subjects, mean, median, standard deviation, minimum, and maximum, lower quartile and upper quartile for continuous variables and using frequency and percentage in each category for discrete variables.

All statistical analyses will be performed using SAS 9.4.

### 11.2.2.2 Test enrollment and completion

Summary the number of subjects who are screened, randomized and completed, the number of subjects in each statistic analysis set will be summarized, the number of subjects discontinued from study and the reason for discontinuation are analysed. Screen failure subjects, discontinued subjects, subjects who are not entered in statistical analysis set will be listed separately.

### 11.2.2.3 Demographic data and baseline characteristics

Describe the demographic characteristics (age, gender, etc.), baseline information, as well as medical history, and evaluate the comparability of the baseline information among treatment groups.


#### 2) Secondary endpoint analysis

Secondary endpoint will use the same method as the primary endpoint, statistically analyzed was the change from baseline in HAM-D17 total score, HAMA total score and SDS total score.

The change in HAM-D17, HAMA, and SDS total score and each item score from baseline will be summarized, Paired t test will be used for statistical comparison. Analysis of variance (ANOVA) was used for statistical comparison of treatment groups.

The change in CGI-S score from baseline will be summarized, Wilcoxon-Signed Rank Test will be used to statistical comparison. Cochran-Mantel Haenszel test stratified by site will be used to statistical comparison.

The change in CGI-I score from baseline will be summarized, Cochran-Mantel Haenszel test (CMH-) stratified by site will be used to statistical comparison.

Summary the response rate of MADRS, HAM-D17, and remission rate of MADRS, HAM-D17 at the different time point before and after the treatment. Clopper-Pearson was used to calculate 95% confidence interval. CMH- test stratified by site was used to statistical comparison.

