#### **4.5 Sample size estimate**

Sample size estimate were based on the primary efficacy endpoint, MADRS total score change from baseline, based on phase II clinical trial result, a standard deviation of 9 units was selected based on the MADRS score change from baseline at the end of treatment. Statistically significant

was 5% level on two side with a power of 90%. Active treatment group was significantly different from the placebo group with a mean different of -3.5 units, Subjects were randomly 1:1:1 assigned to 80mg group, 160 group and placebo group. PASS15 software was used to calculate the sample size, 140 patients per group. Considering about 25% drop-out rate, 186 subjects were planned in each group, total 558 subjects in three groups.

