#### **4.6 Randomization method**

Dynamic randomization will be applied, the randomization will be conducted by the minimization random allocation system. Pocock&Simon minimization method will be used, baseline MADRS score, age and gender are prognostic factors, and will be taken as stratification factor to make them balance between groups. After qualified subjects recruited, The researcher who involuted in clinical trial will use the specified username and password to log into the system, filled in the screening required information, obtained the random number relevant to certain drug, and then subject will receive the drug based on the randomized number that subject had. The random list will be generated by a third party statisticians using SAS; and the statistician will conduct the procedure of drug blinding set-up and emergency envelope production.

Two copies of randomized drug blinding code shall be kept by the investigator and sponsor for each. The procedure of unblinding will be performed in two levels, first-level unblinding takes place when all data forms have been keyed into the database and database locked, allocation that predetermined by the assignments for each participant who entered into the A, B and C study group are provided, and then statistician will perform the statistical data analysis. Second level of unblinding shall be made after completing the first draft of report of the statistical analysis, and then identify the group A, B and C are corresponded to the study group of 80 mg, 160mg group and placebo group.

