#### **The secondary efficacy endpoint**

- Changes from baseline in the 17 items Hamilton Depression Scales (HAM-D17) total scores at the end of treatment.
- Clinical Global Impression – global improvement (CGI-I) scores at the end of treatment.
- Changes from baseline in the Clinical Global Impression –severity illness (CGI-S) scores at the end of treatment.
- Changes from baseline in the the Hamilton Anxiety Scale (HAMA) total scores and factor scores at the end of treatment.
- Changes from baseline in the HAM-D17 factor scores at the end of treatment.
- Response rate in MADRS at the end of treatment (Response means that the reduction in MADRS score is 50% or more relative to the baseline value).
- Response rate in HAM-D17 at the end of treatment (Response means the reduction in the HAM-D17 scores is 50% or more relative to the baseline values).
- Remission rate in MADRS at the end of treatment (Remission refers to MADRS  $\leq 12$ ).
- Remission rate in HAM-D17 at the end of treatment (Remission refers to HAM-D17  $\leq 7$ ).
- Changes from baseline in the SHEEHAN Disability Scale (SDS) total scores at the end of treatment.

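### The MADRS remission test is stratified by site only and leaves out baseline severity, which costs it a little power (about 0-5 points, mostly 1-3) and makes it slightly conservative

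*Protocol*

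**What the plan says.** Protocol section 11.2.2.4, part 2, summarises MADRS and HAM-D17 response and remission with Clopper-Pearson intervals. For the comparison between arms it states "CMH- test stratified by site was used to statistical comparison". Site is the only stratum named, and no between-arm effect estimate is specified for these rates.

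Three other places bear on this:

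- Section 4.6 sets up Pocock-Simon minimisation: "baseline MADRS score, age and gender are prognostic factors, and will be taken as stratification factor to make them balance between groups". Site is not among the allocation factors.
- Section 11.2.2.4, part 1, includes baseline MADRS as a covariate in both the primary MMRM and the sensitivity ANCOVA.
- Section 8.1 defines remission by a fixed score: "Remission rate in MADRS at the end of treatment (Remission refers to MADRS" at or below 12), and HAM-D17 at or below 7. Response is a fall of at least 50% from the patient's own baseline.

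Section 5.1 requires a MADRS total of at least 26 at screening and sets no upper limit.

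**The concern.** The distance to a fixed cut-off grows with the starting score. A patient who starts at MADRS 27 needs a fall of 27 - 12 = 15 points to remit; one who starts at 40 needs 40 - 12 = 28. If the final score depends on baseline at all, so does remission.

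The allocation scheme balances baseline MADRS across arms, so chance imbalance in it contributes little to the observed difference in remission. A test that ignores baseline still counts that variation in its standard error. The standard error is then somewhat too large, the test rejects a true null less often than its nominal level, and it misses a real benefit more often than it needs to.

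What is at stake is efficiency on secondary endpoints. The continuous scores are adjusted for a prognostic variable recorded at entry, while remission on the same scale is not.

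**Working it through.** **1. The plan's own figure.** Section 4.5 gives the inputs: "was 5% level on two side with a power of 90"%, "a standard deviation of 9 units was selected", "mean different of -3.5 units", and 1:1:1 allocation.

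n per arm = 2 x (1.960 + 1.282)^2 x 9^2 / 3.5^2 = 2 x 10.51 x 81 / 12.25 = 139. With the noncentral t distribution it is 140 (power 0.900). Inflated for 25% dropout, 140 / 0.75 = 186.7, against 186 stated. The plan's figures reproduce. It states no power or assumed rates for remission or response.

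**2. Simulation inputs.**

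- From the protocol: 558 patients in three arms, minimisation on baseline MADRS, age and gender, change SD 9, effect -3.5, entry at MADRS 26 or more, remission at 12 or less, response at a 50% fall or more.
- Assumed, because the protocol does not give them: 20 sites with no true site effect (10-40 tried), mean placebo change -13 (-11 and -16 tried), baseline SD after truncation at 26 of 3.2, 4.4 or 5.7, and slope b of final score on baseline of 0.4, 0.7 or 1.0.

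With the SD of change fixed at 9, the implied baseline-final correlation is r = b*s / sqrt(81 - (1-b)^2*s^2 + b^2*s^2), where s is the baseline SD. For example, b = 1.0 and s = 5.7 give 5.7 / sqrt(81 + 32.5) = 0.54.

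**3. Like-for-like comparison.** The site-stratified CMH test was set against a site-adjusted logistic score test, corrected for degrees of freedom, first without and then with baseline. Without baseline the two agreed to within 0.1 points, so the differences below come from baseline alone. Power for MADRS remission, one dose against placebo:

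| Baseline SD | Slope | r | 186/arm: CMH -> with baseline | About 140/arm: CMH -> with baseline |
|---|---|---|---|---|
| 3.2 | 0.4 | 0.14 | 80.8 -> 81.0 (+0.2) | 68.8 -> 69.0 (+0.2) |
| 3.2 | 0.7 | 0.24 | 78.6 -> 79.6 (+1.0) | 65.5 -> 66.6 (+1.1) |
| 3.2 | 1.0 | 0.34 | 77.0 -> 78.5 (+1.5) | 64.5 -> 66.9 (+2.4) |
| 4.4 | 0.4 | 0.20 | 78.5 -> 79.4 (+0.9) | 66.8 -> 67.4 (+0.6) |
| 4.4 | 0.7 | 0.33 | 76.2 -> 78.3 (+2.1) | 58.6 -> 60.4 (+1.8) |
| 4.4 | 1.0 | 0.44 | 71.8 -> 75.2 (+3.4) | 59.0 -> 62.4 (+3.4) |
| 5.7 | 0.4 | 0.26 | 77.7 -> 79.2 (+1.6) | 65.6 -> 66.2 (+0.6) |
| 5.7 | 0.7 | 0.41 | 71.2 -> 73.8 (+2.7) | 57.6 -> 60.6 (+3.0) |
| 5.7 | 1.0 | 0.54 | 67.7 -> 73.2 (+5.4) | 53.5 -> 58.6 (+5.1) |

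Powers are in percent and gains in points, taken from unrounded values. A further simulation with other settings gave about 0.5-4.5 points for r of 0.2-0.5, and 6.5 points at r = 0.56.

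**4. Type I error.** For MADRS remission the site-only CMH test ran at 0.035-0.048 against 0.05, lowest where r was highest (0.0348 at r = 0.54). For response it ran at 0.046-0.050.

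**5. Response.** The required fall scales with baseline, so little is left for baseline to explain. The gain was about 0-2 points: for example 83.7 -> 83.7 at SD 4.4 and slope 0.7, and 80.4 -> 82.0 at SD 5.7 and slope 1.0 (both 186/arm).

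**6. Baseline category as an extra CMH stratum.** Crossing site with two severity levels changed remission power by about -4.6 to +1.2 points, because many cells become too small to contribute.

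**The case against.** The case for leaving the plan alone is fair on several counts. A pre-specified site-stratified CMH test is valid and errs on the safe side. The step-down procedure in section 11.2.2.6 covers only the MADRS change score, so no controlled claim rests on these rates. The primary analysis already adjusts for baseline. Response is barely affected. HAM-D17 remission was not simulated, and baseline HAM-D17 is not a minimisation factor. All of this stands, and it limits the point to a small efficiency gain on MADRS remission.

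A reader might infer a larger loss, such as 3-10 points as the usual case. The documents do not support that, because they supply none of the inputs that would fix such a figure. Gains of that size also depend on choices that do not isolate baseline: letting simulated patients start below 26, assuming no regression to the mean or less improvement in sicker patients, or comparing the CMH test with a model test that also drops the site strata or lacks a small-sample correction. An uncorrected logistic test ran at about 5.3-5.7% under the null, so part of its apparent gain is excess type I error.

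It can also be said that baseline is not wholly ignored, because section 11.2.2.7 fills missing remission outcomes from the MMRM, which contains baseline. That affects the imputed values. It does not put baseline into the test, so the observed outcomes are still compared unadjusted.

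Nor is this a detail left to a statistical analysis plan: the protocol names the test and its only stratum.

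**Conclusion.** The point holds as an optional improvement for MADRS remission. Leaving out baseline costs about 0-5 points of power, mostly 1-3, and the test runs at about 3.5-5% instead of 5%. A loss above 5 points needs a baseline-final correlation above about 0.5. These figures rest on an assumed baseline SD, slope, placebo change and number of sites. The direction follows from the absolute cut-off and the minimisation, provided that baseline predicts the final score, which section 4.6 itself asserts by calling it prognostic.

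The protocol does not contradict itself here, and no result would be invalid under the current wording. The same reasoning applies in kind to HAM-D17 remission, but no size is claimed for it.

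**What to change.** In section 11.2.2.4, part 2, make the main comparison of each remission rate a logistic regression with treatment, site (small sites pooled by a stated rule) and the continuous baseline score of the same scale. Use the same model for the response rates for consistency. Report the covariate-standardised risk difference of each dose against placebo with its 95% CI, which also supplies the between-arm estimate that the section now lacks. Keep the site-stratified CMH test as supportive. Do not add baseline category to site as a CMH stratum, for the reason in step 6 of the working.

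The cost is about one sentence in the protocol and a short SAS model call on data already collected, provided that the change is made before unblinding. There are two small downsides. The odds ratio becomes conditional on baseline, which is why the standardised risk difference should be the reported effect. With many small unpooled sites the model can run slightly above the nominal level (5.1-6.2% in one simulation), which is why small sites should be pooled.

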#### **11.2.2.5 Safety evaluation**

Adverse events will be coded using MedDRA. The statistical analysis will be focus on treatment emergent adverse events (TEAE), The adverse events that occurred from the screening to the first dose will be presented by listing, but not included in the statistical analysis of adverse events. Adverse events mentioned in the following paragraphs are all for TEAE.

All adverse events, adverse events related to the study drug, adverse events unrelated to the study drug, serious adverse events, and adverse events leading to withdraw will be summarized, number of subjects, frequency and percentage of subjects will be calculated, Fisher exact test will be used for statistical comparison. The TEAE and related TEAE categorized by SOC and PT will be summarized by treatment group. All adverse events, adverse events related to the study drug, adverse events unrelated to the study drug, serious adverse events, and adverse events leading to withdraw will also be presented by listings.

Shift tables will be used to summarize the clinical significance evaluation of laboratory and ECG parameters, and all abnormal parameters with clinical significance will be listed.

#### **11.2.2.6 Multiplicity**

In order to control the type I error in the multiple comparisons, a step-down process was used to compare the change in MADRS total score from baseline at week 8 between each dose group (80mg, 160mg) with placebo, which is that comparison was performed for the 160 mg group first and, if the different is statistically significant, the comparison will be performed subsequently in the 80mg group. Otherwise, no comparison will be performed in the 80mg group.

The result for safety evaluation, P-value is the nominal P value, P-value is used to describe the relationship between safety endpoint and treatment groups and will not be used for formal

statistical inference.

#### **11.2.2.7 Processing of missing data**

The Mixed-Effect Model Repeated Measure (MMRM) will be used to analysis the total score of MADRS, HAM-D17, HAMA and SDS for missing data. The LOCF methods was used to impute the missing data and ANCOVA model was used for sensitivity analysis.

For MADRS response rate, HAM-D17 response rate, MADRS remission rate and HAM-D17 remission rate, the predicted value from MMRM model will be used to imput the missing data, and this analysis will be considered as primary analysis results.

The analysis results of the MADRS response rate, HAM-D17 response rate, MADRS remission rate, HAM-D17 remission rate based on the LOCF imputation will be considered as sensitivity analysis.

The rest of endpoints efficacy evaluation, including HAM-D17 single item scores, HAMA single item scores, CGS-S score, CGS-I score, the LOCF method was used to impute the missing data.

This study will not perform any missing data imputation for safety endpoint.

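### Filling missing response and remission status from a single MMRM prediction makes the CMH tests of these four secondary rates anti-conservative

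*Protocol*

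**What the plan says.** Protocol section 11.2.2.7 deals with missing status for the MADRS and HAM-D17 response and remission rates. It says that "the predicted value from MMRM model will be used to imput the missing data, and this analysis will be considered as primary analysis results", and it names LOCF as the sensitivity analysis. It mentions no residual draw, multiple imputation or variance correction. It does not say whether the prediction is subject-level or uses fixed effects only.

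The cut-offs are in section 8.1. For MADRS, "Response means that the reduction in MADRS score is 50% or more relative to the baseline value"; HAM-D17 response is defined likewise. Remission is a MADRS total of 12 or less, or a HAM-D17 total of 7 or less.

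Section 11.2.2.4 gives the rates Clopper-Pearson intervals and compares arms with a CMH test stratified by site. The full analysis set in section 11.2.1 requires a baseline score and one dose, but no post-baseline score. Section 4.5 sets the amount of missing data to expect: "Considering about 25% drop-out rate, 186 subjects were planned in each group". The step-down in section 11.2.2.6 covers only the week-8 MADRS change. That section labels the safety p-values as nominal but says nothing of the kind about the rates.

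**The concern.** An MMRM prediction is a conditional mean. Real week-8 scores scatter around it, and the predictions for dropouts do not. When a 50% or fixed-score cut is applied, the dropouts of an arm cross the threshold together more than real patients would. The prediction also contains the estimated arm-by-visit effect, so a chance difference among the observed patients is copied into the dropouts. The CMH test then counts those copies as independent observations.

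With 186 per arm and 25% dropout, 0.25 × 186 = 46.5, so about 46 or 47 statuses per arm would be filled this way. What is at stake is the error rate and size of four efficacy results that readers commonly use to judge clinical benefit.

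**Working it through.** **The plan's own figure first.** Inputs from section 4.5: two-sided 5%, power 90%, SD 9 ("a standard deviation of 9 units was selected based on the MADRS score change from baseline at the end of treatment"), difference 3.5 ("with a mean different of -3.5 units"), allocation 1:1:1.

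- n = 2(z₀.₉₇₅ + z₀.₉₀)² SD²/δ² = 2 × (1.960 + 1.282)² × 81/12.25 ≈ 139. The t-based value is 140 (power 0.9002), which agrees with "PASS15 software was used to calculate the sample size, 140 patients per group".
- 140/0.75 = 186.7, so 187 against the stated 186. The difference is immaterial. The Protocol states no error rate for the imputed rates.

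**Hand check of the mechanism.** With a true rate near 0.5, the test's nominal SD for a rate difference is √(2 × 0.5 × 0.5/186) = 0.052. In a simulation with no treatment effect and an arm mean change of -16.5, the SD after single-prediction imputation was 0.066. The test's critical value of 1.96 nominal SDs is then only 1.96 × 0.052/0.066 = 1.54 true SDs. The two-sided rejection rate is about 12%, close to the 13.1% simulated in that case.

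**Simulation of the null rejection rate.** Taken from the Protocol: three arms of 186, 25% dropout, SD of week-8 change 9, and arm and baseline effects by visit. Assumed, because the Protocol does not give them:

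- baseline mean 32, SD 4, floor 26
- mean change -12 to -20
- visit correlation autoregressive 0.8 or 0.9, or constant 0.5
- 15 sites where the CMH test was run; a pooled z test otherwise
- dropout timing and mechanism

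The table shows runs with subject-level prediction, autoregressive correlation, random dropout and the pooled z test. MI means 20 draws with residual and parameter uncertainty, dichotomised per data set and combined by Rubin's rules. Each pair is response / remission on the MADRS scale.

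| Mean change | Some dropouts without post-baseline score | Null rejection, single prediction | Null rejection, MI | Rates, full data | Rates, single prediction |
|---|---|---|---|---|---|
| -12 | no | 7.6% / 6.0% | 2.7% / 2.9% | 33.9% / 21.1% | 30.8% / 17.9% |
| -14 | no | 9.1% / 7.3% | 3.0% / 3.6% | 42.3% / 27.6% | 40.1% / 24.2% |
| -16 | no | 13.1% / 8.7% | 4.7% / 4.0% | 51.1% / 35.2% | 50.5% / 32.0% |
| -18 | no | 10.5% / 9.7% | 2.8% / 4.1% | 59.7% / 43.3% | 60.8% / 40.9% |
| -16, correlation 0.9 | no | 8.5% / 7.4% | 4.0% / 2.8% | 51.1% / 35.2% | 50.6% / 33.4% |
| -14 | yes | 9.1% / 6.8% | 3.3% / 2.4% | 42.3% / 27.6% | 38.6% / 23.6% |
| -16 | yes | 21.6% / 9.2% | 2.6% / 3.5% | 51.1% / 35.1% | 50.2% / 31.1% |
| -18 | yes | 13.3% / 12.0% | 4.8% / 4.3% | 59.8% / 43.4% | 62.4% / 40.2% |

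The first four rows use 1,500 trials each and the others 800. The Monte Carlo standard error at 13.1% is √(0.131 × 0.869/1500) = 0.9 points. At 21.6% with 800 trials it is 1.5 points.

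Over all scenarios run:

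- Every dropout with a post-baseline visit: response 7.6 to 13.1%, remission 6.0 to 9.7%.
- Some dropouts without one: response 7.3 to 25.8%, remission 5.7 to 12.0%.
- A second simulation under similar assumptions: response about 7.5 to 15%, remission 6 to 9%.
- Mean change -16 with 10% or 15% dropout: response 11.2% or 13.0%, remission 6.3% or 6.9%.
- Fixed-effects-only prediction: from about 5% up to 50%, worst with the arm mean near the cut-off.
- Full data, LOCF and non-responder imputation: all near 5%.

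**With a true 3.5-point effect** (mean changes -13 and -16.5), the response difference is 53.2 - 38.0 = 15.2 points in full data and 52.1 - 32.9 = 19.2 points after single prediction. The second simulation gave 17.3 against 14.8. The remission difference is hardly changed: 32.8 - 20.1 = 12.7 against 37.2 - 24.1 = 13.1.

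The dropouts explain the excess. For mean changes of -14.5 and -18, 36% and 67% of dropouts are called responders, against true values of 43% and 59%. The arm difference among them is 31 points instead of 16, and 0.25 × (31 - 16) = 3.75 points.

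**The case against.** **The word primary.** A reader might infer that the trial's primary result is damaged. It is not. These rates are listed as secondary in section 8.1 and lie outside the step-down in section 11.2.2.6. The confirmatory MADRS change test, its sample size and its error control are untouched. This lowers the severity.

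**The figures are not the Protocol's.** This is true. They depend on assumed values, and the largest arise when the arm mean sits near the 50% cut. Phase II MADRS mean changes at week 6 ran from -10.92 to -15.65. At a mean change of -11, response inflation was 8.0%. The exact size is therefore open, but every response scenario with subject-level prediction exceeded 5%.

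**Exaggeration is not general.** This also stands. Bias in the response rate ran from about -4 to +3.5 points and was near zero when the mean change was close to the cut-off. Remission rates were about 1.5 to 5 points too low, and the remission difference was not overstated in the effect scenario.

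**LOCF as a safeguard.** A reader might infer that LOCF shares or hides the defect because it too is a single imputation. In the simulations it held about 5%, so a disagreement with it would be a useful warning. It has its own bias, however, and is not the designated main result.

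**Gaps in the check.** HAM-D17 was not simulated, and Clopper-Pearson coverage was not computed. The extension to HAM-D17 rests on the shared mechanism, and no claim about the width of those intervals is made here. The analysis plan, not shown, may say which prediction is meant. To remove the problem, however, it would have to depart from the stated rule of imputing the predicted value.

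**Conclusion.** The rule as written gives the CMH tests of the response and remission rates a false-positive rate above the nominal 5%. With subject-level prediction and 25% dropout, it is roughly 7 to 13% for MADRS response, rising to about 26% when some dropouts have no post-baseline score, as the full analysis set allows. For MADRS remission it is roughly 6 to 12%. A fixed-effects-only prediction could be worse. The rates are off by a few points, with a sign that depends on the arm mean relative to the cut-off. With a true 3.5-point effect near the cut-off, the response difference is about 17 to 19 points against 15.

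The direction follows from the method. The size rests on the assumed baseline, mean change, correlation and dropout timing. This should be fixed, but it does not threaten the primary conclusion.

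**What to change.** In section 11.2.2.7, replace the single predicted value with multiple imputation from the same MMRM, using draws that include residual and parameter uncertainty. Dichotomise within each imputed data set. Combine the site-stratified rate difference, or a suitably transformed CMH statistic, by Rubin's rules, and state this in section 11.2.2.4. Fix the number of imputations in advance; the check used 20.

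One stochastic draw would not be enough. It nearly restores the rates but still treats imputed statuses as observed: at 10% dropout and mean change -16, null rejection for response was 6.8% against 5.5% with full data.

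Non-responder imputation may be added as a sensitivity analysis alongside LOCF.

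The cost is revised wording and a standard program, with no new data or patients. In the check, multiple imputation gave 2.4 to 4.8% null rejection and rates within about 1 point of full data. It is thus slightly conservative, and p-values will be somewhat less favourable. The change should be made before unblinding.
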